## Abstract

**Background:**

Depressive disorders are highly prevalent in primary care (PC) and are associated with considerable functional impairment and increased health care use. Research has shown that many patients prefer psychological treatments to pharmacotherapy, however, it remains unclear which treatment is most optimal for depressive patients in primary care.

**Methods/Design:**

A randomized, multi-centre trial involving two intervention groups: one receiving brief cognitive behavioral therapy and the other receiving general practitioner care. General practitioners from 109 General Practices in Nijmegen and Amsterdam (The Netherlands) will be asked to include patients aged between 18-70 years presenting with depressive symptomatology, who do not receive an active treatment for their depressive complaints. Patients will be telephonically assessed with the Structured Clinical Interview for DSM-IV Axis I Disorders (SCID-I) to ascertain study eligibility. Eligible patients will be randomized to one of two treatment conditions: either 8 sessions of cognitive behavioral therapy by a first line psychologist or general practitioner's care according to The Dutch College of General Practitioners Practice Guideline (NHG- standaard). Baseline and follow-up assessments are scheduled at 0, 6, 12 and 52 weeks following the start of the intervention. Primary outcome will be measured with the Hamilton Depression Rating Scale-17 (HDRS-17) and the Patient Health Questionnaire-9 (PHQ-9). Outcomes will be analyzed on an intention to treat basis.

**Trial Registration:**

ISRCTN65811640

## Background

Depressive disorders are highly prevalent in primary care (PC) [1,2] and are associated with considerable impairment in quality of life [3,4], high service utilization use and high medical costs [5]. Most patients with depressive disorders are seen and treated by their general practitioner (GP) [6,7].

The Dutch multidisciplinary guideline (2005) for Major Depressive Disorder (MDD) and the Dutch College of General Practitioners Practice Guideline offer evidence based treatments for PC patients. Two options are available: brief psychotherapy and a minimal intervention by the GP, which may include prescribing of antidepressants. The latter will be referred to as general practitioners care (GPC).

Prescribing of antidepressants is dependent of suffering, dysfunction and the preference of patients. However, research has shown that nowadays many patients prefer psychological treatments to pharmacotherapy [8,9].

Effective psychological treatments, like brief cognitive behavioural therapy (bCBT), for depression are available in PC [10]. However, little is known about the relative effectiveness of a bCBT compared to GPC. This is most likely due to limitations in carrying out bCBT studies in PC. These limitations include for example specialized and standardized training of primary care professionals in the intervention.

In the Netherlands, all inhabitants are enlisted with a GP and have an open and unlimited access to the GP. The GP performs a gatekeeper function which enables him to control access to specialist health care. First line psychologists (FLP) are operating in PC and are often connected to the practices of the GP. They offer generalized psychological care, mostly after referral of a GP, and are easily accessible.

The few studies that are available concerning the benefits of bCBT relative to GPC for treating depression in primary care show conflicting results.

Proutfoot *et al*, Schoenbaum *et al *and Simon *et al *showed benefits of bCBT relative to GPC [11-13], while there is also some evidence showing that bCBT might not be superior to GPC at post treatment [14] and at 12-month follow-up [15].

## Methods/Design

### Objective

The aim of this paper is to present the research protocol of our randomized trial designed to compare a protocolized brief CBT (bCBT) performed by a FLP with a treatment performed by a general practitioner (general practitioners care; GPC) for primary care patients with MDD. We hypothesize that bCBT will be superior to GPC.

### Design and setting

Primary care patients with MDD will be randomized to either an eight session bCBT or GPC of 12 weeks duration.

The study will be conducted in 109 General Practices in two regions connected to academic settings in The Netherlands: the Academic Medical Center in Amsterdam and the Radboud University Nijmegen Medical Center in Nijmegen.

### Inclusion criteria

Patients aged between 18 and 70 years and suffering from MDD as determined by an independent researcher with the Structured Clinical Interview for DSM-IV Axis I Disorders (SCID-I) [16,17].

### Exclusion criteria

- Suffering from schizophrenia or bipolar disorder (now and in the past as assessed by the SCID-I).

- Contra-indication for MDD treatment like mental retardation or terminal illness.

- Insufficient comprehension of the Dutch or English language.

- Severe suicidal thoughts.

- Receiving an active MDD treatment. Active treatment is defined as:

- Antidepressive medication (except those who receive this in low dosage for pain complaints or as an anti-smoking intervention: Amitriptyline ≤ 50 mg, Nortriptyline ≤ 50 mg, Zyban (bupropion)).

- Psychotherapy.

- Supportive consultations by the GP or social worker, except for diagnostic visits to complete the diagnosis (≤ 2).

### Recruitment of patients and baseline assessment

GPs will be asked to include patients whom they consider to be suffering from MDD. Patients identified by their GP as suffering from MDD will receive information regarding the study and are asked to fill out the Patient Health Questionnaire (PHQ) [18]. Within 3 days after inclusion by the GP, a researcher will contact the patient by telephone to provide further explanation and seek informed consent regarding the diagnostic phase of the study. Consenting patients will be further assessed with a telephonic SCID-I interview. If the patient fulfills the DSM-IV criteria for MDD, subsequent SCID-I sections will be checked to assess eligibility. When eligible, the patient will be further assessed with a baseline Hamilton Depression Rating Scale-17 (HDRS-17) [19] to establish the severity of the depression. At the end of the telephonic assessment the patient receives the results of the interview and is asked to discuss these results and the treatment options with the GP. All results will also be sent to the GP. During the appointment with the GP the patient will make the decision to enter the trial or not. If the patient agrees to participate in the study, a second informed consent form will be signed and the GP proceeds with the randomisation procedure as described below.

### Randomization

After informed consent, GPs will perform an internet based randomization procedure. A computer program generates a stratified block randomization (block randomization of 4 blocks stratified by gender and location (Nijmegen/Amsterdam)) where the patient is randomized over the two treatment strategies with no preference option. The computer then generates an outcome on the GP's computer screen and simultaneously sends an email of this outcome to the researcher. If the patient is randomized to GPC, the GP will immediately make the first appointment. If the patient is randomized to bCBT the researcher will contact the nearest participating FLP and refer the patient.

### Interventions

#### General Practitioners Care

The treatment protocol is set up in accordance with the Dutch College of General Practitioners Practice Guideline (NHG- standaard) [20] and composed after evaluating the content of colleague general practitioners' (follow up) appointments with depressive patients.

The description of the content of the contacts is meant as a guideline; GP's can adapt the scheme to their own style or to special circumstances. The treatment consists of supportive contacts which can be combined with an antidepressant agent. The duration of the treatment is 12 weeks. The following elements are recommended: psycho-education about depression, life style advices about sleep, alcohol/drugs, nutrition, social activities and physical activities.

The minimum frequency is one contact every two weeks during the first six weeks and one telephonic contact and one face- to- face evaluation contact during the second 6 week period. This can be increased if needed. Reasons for more contacts can be for instance: the severity of the complaints and/or lack of social support. After the first six weeks the GP evaluates, together with the patient, the need and frequency for further contacts. If recovery is not sufficient, according to the patient and/or GP, the GP will offer further contacts, during which problem solving will be a key element. If recovery is substantial the GP will provide information on relapse prevention and will offer contacts by telephone during the next month and one face-to- face contact after six weeks.

See table 1 for an overview of the contents of the GPC.

**Table 1 T1:** Overview of the contents of the GPC

**Session nr**.	Required elements
Contact 1	Discuss the diagnosis, feelings of the patient and psycho-education (with or without an antidepressant agent)
Contact 2	Evaluation, further psycho-education and life style advices.
Contact 3	Evaluation, re-enforcement and follow-up appointments.
	Thereafter if recovery is:
Contact 4+5	Sufficient: contact by telephone to discuss the course and evaluate possible relapse. Insufficient: evaluation, reinforcement and problem solving
Contact 6	Sufficient: evaluation, relapse prevention Insufficient: evaluation, relapse prevention/offer pharmacological treatment

To monitor the actual content of the provided GPC and potential supplementary treatment, we will sent each GP a short questionnaire at the end of the 12 weeks in which they can state how many appointments they have had with the patient, whether they prescribed an antidepressant (and the dosage) and whether they combined their treatment with a treatment by another health care professional or referred their patient.

In case of randomisation to the FLP, GPs will be asked to fill in a short questionnaire at the end of the bCBT in which they can state whether they combined the bCBT with an antidepressant (and the dosage) and whether they combined the bCBT treatment with a treatment by another health care professional or referred the patient.

### Training

In order to optimise the treatment we will pay each participating GP a visit before the start of the study. During this visit we will explain the treatment protocol, content of the contacts and provide a ring binder with the protocol. They will also be informed about the possibility of consulting an independent physician for questions during the intervention period.

GPs will be instructed to make a call to the researcher if they want to divert from the protocol (for example referring a patient to secondary care or a social worker).

### Brief Cognitive Behavioural Therapy (bCBT)

The treatment will consist of 8 sessions within 12 weeks, each of fifty minutes duration. At the end of each session patients will receive homework assignments. The treatment will be directed at the role of behaviour and thinking in depressive complaints. Behaviour: patients will obtain insight in the role of pleasant activities on mood and subsequently learn to identify and expand potentially pleasant activities. Thinking: patients will obtain insight in the influence of negative thoughts and beliefs on their feelings/mood and subsequently learn to challenge these thoughts and beliefs thereby reducing the impact on their feelings. The patient learns to formulate alternative (rational) thoughts and beliefs. Eventually, the therapy will result in a personal prevention plan.

All therapists are licensed first line psychologists trained in this form of cognitive behavioural therapy. To guarantee quality, the sessions will be audio taped and the integrity of the intervention will be assessed. Also, the therapists will perform the intervention under supervision, which means that the therapists will regularly discuss the sessions with colleagues.

See table 2 for an overview of the contents of the bCBT.

**Table 2 T2:** Overview of the contents of the bCBT

**Session nr**.	Required elements
Session 1	- Psycho- education - Explanation of the relation between pleasant activities and mood - Explanation of registration activities - Homework
Session 2	- Review homework assignment - Identification and expanding of potentially pleasant activities. - Explanation of the relation between cognitions and feelings. - Explanation 3 columns - Homework
Session 3	- Review homework assignment - Explain challenging negative thoughts/formulating rational thoughts - Explanation 5 columns - Homework
Session 4	- Review homework assignment - Explain challenge tactics again. - Explanation 7 columns - Homework
Session 5	- Review homework assignment - Practice challenging negative thoughts/formulating rational thoughts - Optional: explanation of schema's - Homework
Session 6	- Review homework assignment - Explanation and challenging of schema's - Homework
Session 7	- Review homework assignment - Prevention plan - Homework
Session 8	- Review homework assignment - How further and prevention plan. - Evaluation and farewell.

### Training

The FLPs will be trained in the treatment protocol by an experienced cognitive behavioural therapist during a two day course. After this course a booster session is planned (by then all therapist have performed at least one 8- session treatment) where problems and questions encountered during the treatment will be addressed.

### Assessments

Patients will be assessed on four occasions: at study entry (t0), 6 weeks after the start of the intervention (t1), at the end of the intervention period (i.e. 12 weeks after the start of the intervention (t2)) and at 52 weeks after the start of the intervention (follow-up assessment;t3).

Assessments will be performed by experienced research interviewers who are blind for the type of treatment given. If a patient drops out of treatment an exit assessment with the outcome measure (see paragraph primary outcome measures) will be completed if possible. The following socio- demographic data will be collected: sex, age, ethnicity, marital status, education, primary role and living situation.

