### Data analysis

We will compare the groups at baseline on socio- demographic characteristics, and functional and clinical data to check whether the randomization has been successful. The main analyses will be intention to treat.

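### Follow-up visits are counted from the start of treatment rather than from randomisation, so time since baseline can differ by arm and patients who never start have no visit dates

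*Protocol article*

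**What the plan says.** The Assessments section places baseline (t0) at study entry and times every later visit from treatment start: "6 weeks after the start of the intervention (t1), at the end of the intervention period", then "12 weeks after the start of the intervention (t2)) and at 52 weeks after the start of the intervention (follow-up assessment;t3". The abstract uses the same origin, with visits "scheduled at 0, 6, 12 and 52 weeks following the start of the intervention". No visit is timed from randomisation.

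According to the section on recruitment and baseline assessment, the HDRS-17 baseline is obtained in the telephone interview. The patient then sees the GP, decides about the trial, and is randomised by that GP.

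The Randomization section describes what follows in each arm:

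- GPC: "If the patient is randomized to GPC, the GP will immediately make the first appointment".
- bCBT: "If the patient is randomized to bCBT the researcher will contact the nearest participating FLP and refer the patient".

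Ethical aspects adds, for bCBT only, a separate consent to audio taping before therapy begins. Neither arm has a stated interval or maximum wait between randomisation and start.

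For patients who stop treatment, Assessments says: "If a patient drops out of treatment an exit assessment with the outcome measure" will be completed where possible. Data analysis commits to analysis as randomised: "The main analyses will be intention to treat".

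**The concern.** Randomisation makes the arms comparable from the moment of allocation. A clock that starts at a later event keeps that comparability only if the event occurs equally soon, and equally often, in both arms. Here the arms reach it differently. A GPC patient is treated by the GP who has just randomised them. A bCBT patient is referred by the researcher to another provider and gives a further consent.

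Two things are at stake.

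1. **Unequal intervals.** The outcomes are symptom scores, response (a fall of at least half from the baseline HDRS-17) and remission. All can change with time whatever the treatment. If one arm is measured later after baseline, part of any difference may reflect elapsed time. If the later arm is bCBT, and patients tend to improve while waiting, the error favours the arm hypothesised to be superior, in a trial powered with a one-sided test.

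2. **Patients without a clock.** A randomised patient who never begins treatment has no start date, and so no defined t1, t2 or t3. The analysis is meant to include that patient, but the schedule does not say when to measure them.

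**Working it through.** **Where the intervals can differ.** Time from baseline to a visit has three parts: baseline to randomisation, randomisation to treatment start, and start to visit. The first precedes allocation and should balance between arms. The third is fixed at 6, 12 or 52 weeks. Only the second can differ systematically, and it is the part with no stated limit.

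**Calendar effect.** Let L be the extra wait in the bCBT arm, in weeks, and suppose GPC starts at once. The visits, in weeks after randomisation, are:

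| L (assumed) | bCBT t1 / t2 / t3 | GPC t1 / t2 / t3 |
|---|---|---|
| 1 | 7 / 13 / 53 | 6 / 12 / 52 |
| 2 | 8 / 14 / 54 | 6 / 12 / 52 |
| 4 | 10 / 16 / 56 | 6 / 12 / 52 |

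**Spurious difference.** The documents give no waiting time, rate of improvement or HDRS-17 SD, so all three are assumed: L = 2 to 4 weeks, r = 0.3 to 0.5 points per week, SD = 7. With spurious difference = L × r:

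- low: 2 × 0.3 = 0.6 points; 0.6 / 7 = 0.09 SD
- high: 4 × 0.5 = 2.0 points; 2.0 / 7 = 0.29 SD

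Against the planned effect of 0.50 (Power section), these are 0.086 / 0.50 = 17% and 0.286 / 0.50 = 57%.

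**Sensitivity to the constant rate.** What matters is improvement between the nominal visit week and that week plus L. If recovery has slowed by then to half the assumed rate, the figures halve to 0.3–1.0 points (0.04–0.14 SD). At t3 the comparison is, for example, week 52 with week 54 or 56, where little further change would be expected.

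**Effect on the test.** The article's own figure is 51 per arm for effect 0.50, one-sided alpha 0.05 and power 0.80. The t-test calculation gives 50.15, rounded up to 51, so it reproduces. For a plain two-group comparison at one visit with 51 per arm, and a spurious difference of b SD under no true effect:

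one-sided error = 1 − Φ(1.645 − b / √(2/51)), with √(2/51) = 0.198.

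With a second assumed range of 0.02–0.10 SD per week and L = 2:

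- b = 0.04: 1 − Φ(1.645 − 0.202) = about 7.5%
- b = 0.20: 1 − Φ(1.645 − 1.010) = about 26%

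These compare with the nominal 5%. Counting visits from randomisation makes L, and therefore b, zero. The sample size is unaffected.

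**The case against.** The best defence is that counting from treatment start compares the arms after equal exposure. Both treatments run over 12 weeks, and t2 is meant to mark their end. Counted from randomisation, a delayed bCBT patient would be assessed before finishing. This is a fair reason for the choice, and the cost is real. But it suits a comparison among patients who start. The stated analysis is by assignment, and there the wait is part of the assigned strategy.

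It can also be said that no delay is documented. This stands. In the GPC arm the word immediately describes booking the appointment, not holding it. The Background calls first line psychologists easily accessible and often connected to GP practices, and the nearest participating one is used. A reader might infer that bCBT starts later by design. The text supports only that its route has more steps and no stated limit.

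Three other stronger readings are tempting, and the article does not support them:

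- **That intention to treat is broken.** No sentence removes a non-starter or drop-out from the analysis, and a poor time origin does not prevent analysis as randomised.
- **That the exit assessment replaces t1–t3.** The article does not say so. Four assessments are planned with no exception for those who stop, and the exit assessment reads most naturally as extra data.
- **That the abstract contradicts the body on baseline.** Week 0 in the abstract is shorthand for t0.

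The mixed model is no full answer. As described, it deals with missing values under a missing-at-random assumption. That neither equalises the timing of observed values nor gives a non-starter a visit date.

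**Conclusion.** The concern holds in a limited form. The follow-up clock starts at a post-randomisation event that the arms reach by different routes, with no cap on the wait. Following the schedule as written can therefore produce unequal intervals by arm, and it leaves never-starters without visit dates. Intention to treat is put at risk, no more.

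The size cannot be derived from the article. The range of about 0.09–0.29 SD is an illustration that depends on the assumed wait, a constant rate of improvement and the assumed SD. It shrinks if recovery flattens, matters mainly at t1 and t2, and is probably small at 52 weeks. The direction is also conditional: it favours bCBT only if bCBT starts later and patients improve while waiting. The point deserves attention because the possible error is not negligible beside a planned effect of 0.50 and can be avoided cheaply.

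**What to change.** Schedule t1, t2 and t3 at 6, 12 and 52 weeks after randomisation in both arms. State that every randomised patient is assessed at these dates, whether treatment was started, stopped or finished. State that any exit assessment is additional and does not replace a scheduled visit. Record the date of the first session or contact, and report the delay from randomisation to start by arm.

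The cost is a change of wording and scheduling, with the same number of scheduled visits and the same sample size. The one downside is that some bCBT patients may not have completed all eight sessions at t2. In a comparison by assignment, that is part of the effect of being assigned to bCBT.

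If the present origin is kept to equalise exposure, the minimum is to limit the wait, report it by arm, and define a substitute origin for patients who never start. This is weaker, because it reduces unequal timing without removing it.

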### Eligibility assessment

The *Structured Clinical Interview for DSM-IV Axis I disorders *(SCID-I) is a semi-structured interview designed for diagnosing mental disorders according to DSM-IV criteria. Agreement between diagnoses based on telephone and face to face administration of the SCID-I is good (Kappa = 0.73 (with 90% agreement) [21]. The SCID-I will be administered by researchers that have received a SCID-I training from a professional that received an official SCID training. Throughout the study all interviewers will participate in ongoing training sessions and in monthly consensus meetings to maximize accuracy and consistency in the administration of the SCID-I.

### Primary outcome measures

Primary outcomes will be depressive symptomatology as measured by the patient rated PHQ-9 [22], depression severity as measured by the clinician rated HDRS-17 [19], the proportion of patients achieving response on the HDRS-17 and the proportion of patients achieving remission on the HDRS-17. In accordance with the National Institute of Mental Health criteria [23], response is defined as a ≥ 50% decrease of the baseline HDRS-17 score, remission is defined as a HDRS-17 score ≤7.

